#### **14. CONCOMITANT MEDICATION**

1. Participants should avoid taking any drugs/medications for the duration of the study, unless required for the participant's health.
2. All medications will be recorded on the source document/CRF together with the reason for starting it, the intensity, start date and stop date if applicable.
3. It is the investigator's responsibility to review the on-going eligibility of the participant during the duration of the study.

#### **15. LABORATORY ANALYSIS**

Blood samples of up to 10 mls will be collected at both study visits. If the sample collected is not to be used for B cell analysis all blood will be collected into 'red top' serum separator tubes. If the sample is to be used for B cell analysis any blood sample up to 5ml will be collected into 'red top' serum separator tubes and any sample beyond 5ml will be stored in a heparinised tube for B cell analysis.

Blood samples in the serum separator tubes will be stored at room temperature for up to 60 minutes, and then stored at between 2 to 8°C. Samples collected at each study site will be centrifuged at 3000 rpm for 10 minutes within 24 hours at the study

site and separated into at least 2 aliquots for storage at or below -30°C. Pfizer will coordinate the shipping of the aliquots required for serological analysis from study sites to their laboratories in Pearly River, USA.

### **1. Antibody concentrations and Opsonophagocytic activity**

Antibody concentrations (ELISA or Luminex) and opsonophagocytic activity will be analysed by Pfizer in Pearl River, USA to provide consistency with the original study assays.

Serum concentrations of anticapsular immunoglobulin G (IgG) for all PCV13 serotypes will be identified by ELISA and expressed as micrograms per milliliter. The assay will employ 2 absorbents: a C polysaccharide-containing cell wall extract plus serotype 22F capsular polysaccharide. Serum concentrations of anti-capsular immunoglobulin G (IgG) for further vaccine serotypes may also be evaluated.

Should any of the participants have a PCV13 serotype-specific IgG concentration < 0.35 mcg/ml in the serum obtained at visit 2 his/her parent/legal guardian will be notified and a booster dose of PCV13 will be offered to the participant.

### **2. DNA storage**

DNA will be extracted from blood clots and stored in the biobank of the Oxford Vaccine Centre laboratory at the Centre of Clinical Vaccinology and Tropical Medicine, University of Oxford or at local study sites for later analysis for genetic polymorphisms.

### **3. B cell responses**

B cell responses will be determined in participants enrolled at study sites including Oxford and Southampton. At Oxford this analysis will be conducted on fresh samples. For samples obtained elsewhere the analysis will be conducted at Oxford on frozen samples transferred from the other study sites. Where applicable, the serotype-specific antigen specific B cell response to serotypes including 4, 14, 23F

(present in PCV7) and, 1, 3, 19A (present in PCV13) will be analysed in the Oxford Vaccine Centre laboratory at the Centre for Clinical Vaccinology and Tropical Medicine, University of Oxford by ELISPOT and flow cytometric assays depending on the available volumes of blood.

B cell response data will be summarized descriptively as this procedure will be observational only.

## **16. SAFETY**

### **16.1 Adverse Event (AE)**

**An AE or adverse experience is:**

Any untoward medical occurrence in a patient or clinical investigation participant administered a medicinal product, which does not necessarily have to have a causal relationship with this treatment (the study medication).

An AE can therefore be any unfavourable and unintended sign (including an abnormal laboratory finding), symptom or disease temporally associated with the use of the study medication, whether or not considered related to the study medication.

### **16.2 Adverse Reaction (AR)**

All untoward and unintended responses to a medicinal product related to any dose. The phrase “responses to a medicinal product” means that a causal relationship between a study medication and an AE is at least a reasonable possibility, i.e., the relationship cannot be ruled out.

### **16.3 Medically significant adverse events**

All adverse reactions taking place between Visit 1 and Visit 2 requiring medical consultation with the General Practitioner, Emergency Department, or leading to a subject’s withdrawal (excluding pre-planned visits and GP or Emergency Department

visits for routine medical care) will be considered to be medically significant adverse events.

B cell responses will be determined in participants enrolled at Oxford and, potentially, other study sites according to local arrangements. This analysis will be conducted on fresh or frozen samples at Oxford or other sites. Where applicable, antigen specific B cell responses to vaccines received in the study will be analysed by ELISPOT and flow cytometric assays depending on the available volumes of blood.

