#### **7.6 Visit 2 (28 to 42 Days After Visit 1)**

1. Review the participant's diary data since the previous visit.
2. Based on review of the participant's diary and clinical evaluation, determine whether any unsolicited AEs or serious adverse events (SAEs) have occurred since the last study visit and record them on the CRF.
3. Measure and record the participant's axillary temperature.
4. Ensure the participant continues to meet the criteria for continued participation in the trial.
5. Collect a blood sample (approximately 10 mL).
6. Administer a single intramuscular dose of Repevax or Infanrix-IPV and the MMR vaccine into the deltoid of the left and right upper arm respectively if not already received as part of standard of care.
7. Observe the participant for at least 15 minutes after vaccination for any significant acute reactions. Any AE noted during the observation period should be recorded on the source documents and on the AE section of the CRF.
8. The investigator or an authorised designee completes the CRF and updates the test article accountability records.

The study procedures are summarized in the table below:

|               |             |            |
|---------------|-------------|------------|
|               | 40 months*  | 41 months* |
| Study visits  | V1          | V2         |
|               | Recruitment |            |
| Immunisations | PCV13       | DtaP/IPV   |
|               |             | MMR        |
| Blood samples | √           | √          |

\* Ages are approximate

N.B. Participants in this follow-on study known to have MenC SBA titres < 1:8 at the 13 month blood sample from the original study will be offered an additional dose of MenC vaccine as part of this study. This vaccine is not to be administered concomitantly with PCV13, but can be administered at visit 2 or, if preferred by parents, an additional study visit to administer this vaccine can be performed. This vaccine will not form part of the study assessments.

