## **17. CAUSALITY ASSESSMENT**

The relationship of medically significant AEs to the study medication will be assessed by a medically qualified investigator according to the following criteria:

-Related: If the causal relationship between the IMP and the SAE is at least a reasonable possibility, i.e., the relationship cannot be ruled out.

-Not related: If there is no causal relationship between the IMP and the SAE i.e. the event is caused by something other than the IMP e.g. underlying disease, a concomitant medication.

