### **18.1 Reporting Procedures for Adverse Events**

All AEs occurring in the first 4 days after pneumococcal immunisation, and all medically significant adverse events occurring during the study observed by the investigator or reported by the participant, whether or not attributed to study medication, will be reported on the CRF/source document, including the diary card. Reactions occurring in the first 4 days after immunisation will be divided up into solicited and unsolicited reactions.

Adverse events solicited in the diary card that are ongoing after day 4 (as recorded in the diary card provided) will similarly be recorded in the CRF/source document.

The following information will be recorded for medically significant AEs: description, date of onset and end date, severity, assessment of relatedness to study medication, other suspect drug or device and action taken. Follow up information should be provided as necessary.

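### Protocol 16.3 builds 'medically significant adverse events' from adverse reactions, which contradicts 18.1 and leaves the *Not related* class in section 17 empty

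*Protocol*

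**What the plan says.** The protocol separates two terms. In 16.1 an adverse event is any untoward occurrence, related or not. In 16.2 an adverse reaction is narrower: "a causal relationship between a study medication and an AE is at least a reasonable possibility, i.e., the relationship cannot be ruled out".

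Section 16.3 is headed as a definition of adverse *events* but is written in terms of *reactions*: "All adverse reactions taking place between Visit 1 and Visit 2 requiring medical consultation with the General Practitioner, Emergency Department", or leading to withdrawal, with planned and routine visits left out.

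Three later rules use or overlap this class:

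- **18.1** sets two reporting periods. The first is "All AEs occurring in the first 4 days after pneumococcal immunisation". For the rest of the study it requires medically significant adverse events, and both sets are reported "whether or not attributed to study medication, will be reported on the CRF/source document".
- **17** adds a judgement of cause: "The relationship of medically significant AEs to the study medication will be assessed by a medically qualified investigator". The outcomes are *Related* and *Not related*. Although it concerns medically significant AEs, its two criteria speak of the SAE.
- **18.4** asks the investigator to assign relatedness, among other attributes, to the same two sets of events as 18.1.

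Two visit procedures carry no causality filter. Section 7.4 item 3 has the source document updated at each visit with any adverse event and any medical advice sought. Section 7.6 item 2 has staff at Visit 2 "determine whether any unsolicited AEs or serious adverse events (SAEs) have occurred since the last study visit and record them on the CRF".

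**The concern.** A class of events that is to be sorted by cause should be collected without regard to cause. Section 16.3 makes possible causation a condition of entry. Someone must therefore judge relatedness before an event qualifies, and the protocol names nobody for that earlier judgement. The medically qualified assessor in section 17 would then see a set that has already been filtered.

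At stake is the record of non-serious medical consultations between day 5 and Visit 2. If a site applies 16.3 as written, a GP visit judged unrelated to the vaccine is not a medically significant adverse event. If it applies 18.1, the visit is to be reported. Two sites could each claim to follow the protocol and record different events.

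**Working it through.** The plan gives no figure for this point, so the check is a comparison of the rules followed by a count of days.

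**1. Trace one event.** Take a non-serious GP consultation on day 15, unplanned, not a symptom listed on the diary card, with a causal link to PCV13 ruled out.

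- 16.1: it is an adverse event.
- 16.2: it is not an adverse reaction.
- 16.3: it is therefore not medically significant.
- 18.1: for this class attribution is not to matter, so the event should be reported. With the 16.3 definition substituted, it falls outside the class.
- 7.4 item 3: recorded in the source document.
- 7.6 item 2: recorded on the CRF.

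Sections 16.3 and 18.1 cannot both be followed for this event.

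**2. Repeat with uncertain causality.** If the link cannot be ruled out, 16.2 makes the event a reaction, so 16.3 keeps it. Only events judged unrelated are affected.

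**3. Check for circularity.** The entry test for 16.3, through 16.2, is that a causal link is reasonably possible and cannot be ruled out. The test for *Related* in section 17 is the same. Every event that enters through 16.3 has thus already met the *Related* criterion, and *Not related* has no members. Section 18.4 inherits the problem for medically significant events, because it asks for relatedness on the same set.

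**4. Compare the capture rules after day 4 for non-serious events.**

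- 16.3 taken literally: possibly related events that led to a consultation or withdrawal.
- 18.1: medically significant events whatever their cause, plus diary-card events still ongoing after day 4.
- 7.6 item 2: any unsolicited AE since the last visit, with or without a consultation.
- 7.4 item 3: any adverse event and any medical advice sought, for the source document.

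These are nested rules of different width. Changing one word in 16.3 removes the conflict with 18.1, but 7.4 and 7.6 remain wider than 18.1.

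**5. Count the days.** Inputs: day 0 to day 4 for the first period (18.2.1), assumed to be what 18.1 means by its first 4 days; Visit 2 at 28 to 42 days after Visit 1 (7.5 and 7.6).

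- First period: 4 − 0 + 1 = 5 days.
- Follow-up counted from day 0: 28 + 1 = 29 to 42 + 1 = 43 days.
- Remaining days: 29 − 5 = 24 to 43 − 5 = 38.
- Share: 24/29 = 83% to 38/43 = 88%.

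This is calendar time. The protocol gives no event rates, so it cannot be turned into a number or share of events.

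**The case against.** The strongest reply is that 16.3 is only a definition, while the operative procedures collect events whatever their cause. Section 7.4 item 3 covers exactly the consultations at issue, 7.6 item 2 puts unsolicited events on the CRF, section 18 requires every SAE to be reported, and 8.2 item 4 records the reason for any withdrawal. Section 18.4 also sends events not listed on the diary card to the CRF adverse event form, and that sentence sets no day limit, although 18.1 introduces the solicited/unsolicited split for the first 4 days. On this view a loss occurs only if a site lets the definition override all of these.

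Much of this stands, and it rules out several stronger readings that a reader might infer:

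- *Uncertain events are lost.* They are not, because 16.2 keeps them.
- *Unrelated events drop out of the trial record.* This is not established, because the visit procedures may still capture them.
- *The medically significant class is the only rule in section 18 for non-serious events after day 4.* It is not. Section 18.1 also follows diary-card events that are ongoing, and 18.4 may reach further.
- *Between 83% and 88% of the safety data are at risk.* The figure measures days and not events.
- *Adverse event rates cannot be compared between sites.* Section 19 plans no such comparison.

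The reply does not remove the contradiction. The wider rules in 7.4 and 7.6 do not say which events belong to the medically significant class, and that class is what sections 17, 18.1 and 18.4 rely on for reporting and causality assessment.

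**Conclusion.** The contradiction is real and visible in the text. Section 16.3 limits a class to possibly related events, 18.1 demands the same class regardless of cause, and section 17 offers an outcome that no event entering through 16.3 can have. The documents support an inconsistency in the capture rule for events judged unrelated. They do not support a claim that such events are certainly lost.

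The reach is limited to unsolicited, non-serious safety data after day 4. The primary endpoint is IgG in blood taken at Visit 1 before the PCV13 injection, so it is untouched. Local and systemic reactions are collected on the diary card from day 0 to day 4, when all AEs are reportable. SAE reporting has no causality filter. Section 19.4 plans no analysis that depends on the affected class by name.

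This is a moderate correction and not one on which the trial's conclusions turn. The judgement assumes that sites apply 16.3 as worded when they decide what is medically significant. How many events that changes cannot be estimated from the protocol.

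**What to change.** 1. In 16.3, replace *All adverse reactions* with *All adverse events*. This aligns the definition with its heading and with 18.1, and gives section 17 a set in which both outcomes are possible.
2. Reconcile 7.4 item 3, 7.6 item 2, 18.1 and 18.4 so that one rule states which events from day 5 to Visit 2 go on the CRF. If the source document is meant to hold more than the adverse event form, say so.
3. In section 17, replace *the SAE* with *the AE* in both criteria, so that they match the events the section says it assesses.

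The cost is a wording amendment and possibly a few more adverse event entries on the CRF. No visit, sample, endpoint or analysis changes.

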#### **16.4 Unexpected Adverse Reaction**

An adverse reaction, the nature or severity of which is not consistent with the summary of product characteristics.

#### **16.5 Serious or Severe Adverse Events**

To ensure no confusion or misunderstanding of the difference between the terms “serious” and “severe”, which are not synonymous, the following note of clarification is provided:

The term “severe” is often used to describe the intensity (severity) of a specific event (as in mild, moderate, or severe myocardial infarction); the event itself, however, may be of relatively minor medical significance (such as severe headache). This is not the same as “serious,” which is based on patient/event outcome or action criteria usually associated with events that pose a threat to a patient’s life or functioning. Seriousness (not severity) serves as a guide for defining regulatory reporting obligations.

#### **16.6 Serious Adverse Event or Adverse Drug Reaction**

A serious adverse event (experience) or reaction is any untoward medical occurrence that at any dose:

- Results in death,
- Is life-threatening,

NOTE: The term “life-threatening” in the definition of “serious” refers to an event in which the patient was at risk of death at the time of the event; it does not refer to an event which hypothetically might have caused death if it were more severe.

- Requires inpatient hospitalisation or prolongation of existing hospitalisation,
- Results in persistent or significant disability/incapacity, or
- Is a congenital anomaly/birth defect.

Medical and scientific judgment should be exercised in deciding whether an adverse event is serious in other situations.

### **16.7 Expected Adverse Reactions**

For all expected adverse reactions see summary of the product characteristics for each vaccine.

### **16.8 Suspected Unexpected Serious Adverse Reactions (SUSAR)**

A serious adverse reaction, the nature or severity of which is not consistent with the applicable product information.

## **17. CAUSALITY ASSESSMENT**

The relationship of medically significant AEs to the study medication will be assessed by a medically qualified investigator according to the following criteria:

-Related: If the causal relationship between the IMP and the SAE is at least a reasonable possibility, i.e., the relationship cannot be ruled out.

-Not related: If there is no causal relationship between the IMP and the SAE i.e. the event is caused by something other than the IMP e.g. underlying disease, a concomitant medication.

## **18. REPORTING PROCEDURES FOR SERIOUS ADVERSE EVENTS**

All Serious Adverse Events (SAEs) must be reported to the CI and sponsor (University of Oxford Clinical Trials and Research Governance Office) within one working day of discovery or notification of the event. All SAE information must be recorded on a SAE form and faxed or a scanned copy emailed to the sponsor.

In addition, SAEs that are experienced by participants taking a Pfizer product must also be reported to Pfizer within one working day of discovery or notification of the event. The SAE must be recorded on the SAE form belonging to the manufacturer to whom it will be faxed or scanned copy emailed.

Additional information received for a case (follow-up or corrections to the original case) need to be detailed on a new SAE form and faxed to the sponsor and to Pfizer

The CI, in conjunction with Pfizer, will report suspected adverse reactions which are both serious and unexpected (SUSARs) experienced by participants taking a Pfizer product to the Competent Authorities (MHRA) and the REC that gave a favourable opinion for the study.

Fatal or life-threatening SUSARs must be reported within 7 days and all other SUSARs within 15 days. In addition to the expedited reporting above, the sponsor/CI shall submit once a year throughout the clinical trial or on request a safety report to the Competent Authority and Ethics Committee.

In addition to the above, the local PI will be responsible for reporting any SUSARs to the relevant NHS Research and Development offices in their area.

The CTRG will ensure that all SAEs are reviewed by medical monitors on a weekly basis and at the next meeting of the University of Oxford Trials Safety Group (TSG), who will meet at regular intervals and consider:

- Occurrence and nature of adverse events
- Whether additional information on adverse events is required
- Consider taking appropriate action where necessary to halt trials
- Act / advise on incidents occurring between meetings that require rapid assessment (e.g. SUSARs).

### **18.1 Reporting Procedures for Adverse Events**

All AEs occurring in the first 4 days after pneumococcal immunisation, and all medically significant adverse events occurring during the study observed by the investigator or reported by the participant, whether or not attributed to study medication, will be reported on the CRF/source document, including the diary card. Reactions occurring in the first 4 days after immunisation will be divided up into solicited and unsolicited reactions.

Adverse events solicited in the diary card that are ongoing after day 4 (as recorded in the diary card provided) will similarly be recorded in the CRF/source document.

The following information will be recorded for medically significant AEs: description, date of onset and end date, severity, assessment of relatedness to study medication, other suspect drug or device and action taken. Follow up information should be provided as necessary.

### **18.2 Solicited Reactions**

This refers to terms/symptoms that are pre-listed in the diary card. Solicited reactions are those that have previously been reported with the use of the study vaccines and, unless stated otherwise, will be considered related to the vaccine.

Solicited reactions will be recorded and monitored by the parent/legal guardian on the diary card provided by the study team from the day of immunization until Day 4 post-immunisation with the PCV13 booster vaccine.

### **18.2.1 Local Reactions**

Local injection site reactions (redness, swelling and tenderness) at the site of PCV13 booster injection will be monitored daily for 4 days (day 0 to day 4) after each vaccination. An end date will be recorded for any reactions persisting after day 4.

### **18.2.2 Redness and Swelling**

Redness and swelling will be measured and recorded on the diary card. They will be categorized as absent, mild, moderate and severe based on the scale given below. A ruler will be given to the parent/legal guardian with instructions for measuring any redness or swelling at the injection site. The parent/legal guardian will be asked to measure the largest diameter of a local reaction and record this in the diary given at visit 1.

|          |                                      |
|----------|--------------------------------------|
| Absent   | No redness or swelling present (0mm) |
| Mild     | 0.5cm to 2.0 cm                      |
| Moderate | 2.5 cm to 7.0 cm                     |
| Severe   | > 7.0 cm                             |

